#### Participants

We will ask members of the three hospital wards in the ENROLE-acute intervention group to participate in the process evaluation. Target groups of the quantitative and qualitative parts are all EPN, members of the interprofessional team, and ward managers. The qualitative part additionally includes people with cognitive impairment and their relatives as well as members of the hospital’s nursing management and nursing development unit. For the eligibility criteria for each target group, please see Additional file 2.

When selecting participants, we will combine different sampling strategies. For all quantitative parts and the qualitative parts on EPN level, we strive to recruit all members of the relevant target groups. For the remaining explorations, we will form subsamples through purposeful sampling. A predefined sampling plan ensures that different forms of cognitive impairment respectively health professions as well as all three clusters are represented in the sample. The targeted sample size will be guided by reaching data saturation.

For recruitment, we will invite members of the target groups both orally and in writing to participate in the study.

#### Data collection and management

We will collect both qualitative and quantitative process data on cluster and individual level at five time points: tp_0_ (before training, internship, and kick-off event), tp_1_ (after training, internship, and kick-off event), tp_2_ (start of the intervention period), tp_3_ (after transfer or discharge of people with cognitive impairment), and tp_4_ (6 months after start of the intervention period).

The qualitative part of the process evaluation comprises individual (EPN, ward managers, members of the nursing management and the nursing development unit) and dyad interviews (people with cognitive impairment and their relatives) as well as moderated and non-moderated focus groups (EPN, members of the interprofessional team). We will collect data face-to-face, by phone or by web-based video conferencing. Nursing researchers trained in qualitative methodology will guide the data collections. We will audiotape and transcribe interviews and group discussions verbatim.

To collect quantitative data, we will use paper-based questionnaires (EPN, members of the interprofessional team, ward managers) and reflection forms (EPN, members of the interprofessional team). A self-generated identification code will allow us to link participants’ data over time. To increase retention, we will use incentives and email reminder. After data entry, we will perform quality and plausibility checks.

For collecting quantitative and qualitative data, we refer to pre-existing and approved instruments. Only if this is not possible, we will use self-developed instruments. We conduct pretests of all instruments to be used.

In addition, we will gather different process documents and materials (e. g., structured notes on recruitment and retention, protocols and attendance lists, teaching and learning materials, and EPN logbooks).

We will store data both pseudonymously (EPN and ward managers) and anonymously (people with cognitive impairment and their relatives, interprofessional team members, and members of the nursing management and the nursing development unit), while documenting the time point and cluster assignment on data sheets. Data protection follows current data protection laws. We will keep paper-based documents under lock. Electronic data will be password-protected. We will store potentially identifying data separate from the rest of the study material. Data will only be accessible to the research team.

#### Data analysis

For analysing the process data, we will use a stepwise approach. First, we will analyse qualitative and quantitative data separately. Subsequently, we will merge data during the interpretation of the results.

For analysing the qualitative data (interviews and focus groups), we will conduct a thematic framework analysis [71] with a deductive-inductive approach based on the logic model. Furthermore, we will use a qualitative content analysis [72] applying a deductive-inductive approach to review the structured process documents and materials as well as open-ended questions in the questionnaires. We will conduct all qualitative analyses in the software MAXQDA [73]. To promote credibility, two persons will analyse data and discuss findings within the research team.

We will analyse quantitative data (questionnaires and reflection forms) by means of descriptive statistics (frequency, distributional location, and spread) using the software IBM SPSS Statistics [74].

We will combine qualitative and quantitative findings regarding key process variables and outcomes incorporated in our logic model.

### Economic evaluation

We will perform a cost-consequence analysis from the hospital perspective [75].

#### Data collection and management

We will use claims data from the hospital to determine the potential cost savings of the intervention. These will be available at the hospital controlling department. This data includes Diagnosis Related Groups (DRG) charges, length of hospital stay, cost weight, gender, and primary and secondary International Statistical Classification of Diseases and Related Health Problems (ICD) diagnoses. The data will be delivered pseudonymously to the evaluators via a secure data exchange platform. In addition, we will collect training costs consisting of salaries of the nursing staff, the costs of the lecturers as well as material costs for premises, catering and travel costs.

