#### Data analysis

In the cost-consequence analysis, we will compare the intervention group with the control group in terms of total inpatient costs, length of hospital stay, and cost weight. We will add the intervention costs (e.g., training costs) to the DRG charges of the intervention group. We will analyse differences (possibly after log-transformation) between the mean total costs using a t-test. In addition, we will perform additional analyses according to gender, age groups, and cost weight using t-test, Mann–Whitney-U-test, and other statistical tests. The analysis will be performed with IBM SPSS [74] and Microsoft Access.

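### The hospital-perspective cost comparison is built on DRG charges, which are what the hospital bills, so it cannot validly show the cost savings of objective (c)

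*Protocol article*

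**What the plan says.** Under Objectives, item (c) is to assess the potential cost savings of the intervention. The Economic evaluation section sets the viewpoint: "We will perform a cost-consequence analysis from the hospital perspective".

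Its Data collection and management subsection names the source: "We will use claims data from the hospital to determine the potential cost savings of the intervention". On the content of those data it says: "This data includes Diagnosis Related Groups (DRG) charges, length of hospital stay, cost weight, gender, and primary and secondary International Statistical Classification of Diseases". On the spending side, "we will collect training costs consisting of salaries of the nursing staff, the costs of the lecturers as well as material costs".

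Its Data analysis subsection fixes the comparison and the arithmetic:

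- Outcomes: "we will compare the intervention group with the control group in terms of total inpatient costs, length of hospital stay, and cost weight".
- Construction of the total: "We will add the intervention costs (e.g., training costs) to the DRG charges of the intervention group".
- Test: "We will analyse differences (possibly after log-transformation) between the mean total costs using a t-test".

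The article mentions no cost accounts, no cost per bed day and no money value for freed bed days. It also does not say how DRG charges change with length of stay.

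**The concern.** From the hospital's perspective, a cost is what the hospital spends on staff, beds, drugs and services. A charge in claims data is what it bills. The plan uses the second in place of the first, then adds real expenditure (training salaries, lecturers, materials) to it and treats the result as total cost.

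The trial's hypothesis is that better care shortens the stay, and the sample size section assumes three days. Shorter stays would save the hospital money mainly through resources not used, and the planned measure does not observe those resources. At stake is one of the three stated objectives, and a result that the Discussion offers for management and policy decisions. The primary outcome and the safety data are not affected.

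**Working it through.** The economic section states no figure to reproduce, so the check is of what the planned formula measures.

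**Step 1: what is estimated.** Per patient, intervention minus control, let ΔR be the difference in DRG charges, ΔC the difference in the hospital's resource cost of inpatient care, and I the intervention cost.

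- The plan's difference in total cost: ΔR + I
- The hospital's difference in cost: ΔC + I
- The hospital's difference in net result (revenue minus cost): ΔR − ΔC − I

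The plan's figure differs from the cost figure by ΔR − ΔC. It is right only if charges move between arms exactly as resource costs do. Against the net result, ΔR has the wrong sign: a higher charge improves the hospital's position but counts as a loss in the plan.

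**Step 2: which way ΔR could move.**

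- The Background expects fewer adverse events. If that means fewer coded diagnoses and a lower charge, the plan reports a saving where the hospital lost income.
- The intervention includes screening and expanded assessment at admission. If that means more coded diagnoses and a higher charge, the plan reports extra cost where the hospital gained income.
- Wards were allocated by ward managers' decision, and the Discussion expects baseline differences. Case mix alone could move charges either way, and the named test on mean costs is a t-test.

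**Step 3: how far bed days count.** Let c be the cost of a bed day and f the unknown share of it that passes into the charge. For a three-day reduction, ΔC = −3c and ΔR = −f × 3c. The plan then shows I − f × 3c, while the cost difference is I − 3c. The plan's sign turns at f = I / 3c.

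**Step 4: illustration.** Inputs from the article: 3 intervention wards × 2 nurses = 6 nurses; 200 h of training, a 10-day internship and fortnightly two-hour coaching for each; 3 × 120 = 360 intervention patients; a three-day reduction. Assumptions not in the article: 8-hour internship days, 13 coaching sessions, EUR 30–60 per hour, EUR 200–800 per bed day.

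Hours: 6 × (200 + 80 + 26) = 1,836, or 1,836 / 360 = 5.1 h per patient. So I = 5.1 × 30 = EUR 153 up to 5.1 × 60 = EUR 306.

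| EUR/h | EUR/bed day | I | 3c | Cost difference (I − 3c) | Plan, f = 0 | f at which sign turns |
|---|---|---|---|---|---|---|
| 30 | 800 | 153 | 2,400 | −2,247 | +153 | 0.06 |
| 40 | 400 | 204 | 1,200 | −996 | +204 | 0.17 |
| 60 | 200 | 306 | 600 | −294 | +306 | 0.51 |

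The article also gives each nurse one day every two weeks for additional activities, without saying whether this is extra cost. If it is (13 days of 8 h assumed), hours rise to 6 × (306 + 104) = 2,460 and I to EUR 205–410. The smallest saving becomes 600 − 410 = EUR 190 and the largest 2,400 − 205 = EUR 2,195. Lecturers, premises, catering and travel would come on top.

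**The case against.** The strongest reply is that a cost-consequence analysis sets several results side by side. Length of stay and cost weight are both listed comparisons, so a shorter stay would not be hidden. That stands: days saved would be reported. They would not be valued in money, and the figure labelled as cost would still be charge-based.

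A reader might go further and infer that the intervention must look dearer by construction. The documents do not support this. They do not say that charges are fixed per case. With planning standard deviations of 18 and 16 days, long stays that alter the charge are plausible, and the sign in the illustration turns once between 6% and 51% of bed-day cost passes into charges. Fewer coded complications or case mix could also lower charges. Only if charges are largely flat per case would the intervention tend to look dearer.

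It can also be said that the article is condensed and that its list of claims items may not be exhaustive. This carries little weight, because the Data analysis subsection itself names DRG charges as the base of the sum. Adding intervention costs to the intervention arm is correct in itself; the fault is in what they are added to.

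Finally, the study is exploratory and at the feasibility stage. That limits the damage, but it does not make revenue a measure of cost.

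**Conclusion.** The concern holds for the cost comparison. As written, it treats billed revenue as the hospital's cost, so it cannot validly show the potential savings in objective (c). This conclusion needs no assumption about unit costs or about how charges follow length of stay; it comes from the perspective and the formula that the article fixes.

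The direction of the error is not determined. It would be wrong to conclude that the result is bound to go against the intervention, or that the economic evaluation yields nothing, since days and cost weight are still compared.

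The euro figures (a resource saving of about EUR 294 to 2,247 per patient against an apparent excess of EUR 153 to 306 with flat charges) show only that the sign can reverse. They rest on an assumed wage, assumed hours and an assumed bed-day cost, on a three-day effect that is itself a planning assumption, and on an incomplete list of intervention costs. They are not an estimate of the true net result.

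**What to change.** - **Economic evaluation, Data collection and management:** add patient-level accounted costs to the request to the controlling department. If these do not exist, request the cost per bed day of the six wards, with a range for the marginal cost.
- **Economic evaluation, Data analysis:** define hospital cost as that resource cost plus all intervention costs (training and internship, coaching, and release days where they are incremental). Report DRG charges separately as revenue, and report the net result as revenue minus cost. Keep length of stay and cost weight as separate consequences.
- **If no resource costs can be supplied:** label the comparison as one of revenue and draw no cost-saving conclusion from it. This needs no new data.

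The price is one further request to a department that already supplies data, and revised wording. Patient-level accounts are preferable. Length of stay times an average bed-day cost only rescales the primary outcome, and an average cost overstates what is saved at the margin, so that route needs a sensitivity range.

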#### Data analysis

In the cost-consequence analysis, we will compare the intervention group with the control group in terms of total inpatient costs, length of hospital stay, and cost weight. We will add the intervention costs (e.g., training costs) to the DRG charges of the intervention group. We will analyse differences (possibly after log-transformation) between the mean total costs using a t-test. In addition, we will perform additional analyses according to gender, age groups, and cost weight using t-test, Mann–Whitney-U-test, and other statistical tests. The analysis will be performed with IBM SPSS [74] and Microsoft Access.

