**Methods:**

We will conduct an exploratory non-randomised controlled clinical trial with accompanying process and cost evaluation with three intervention and three control wards at one university hospital. The person-centred care intervention consists of 14 components reflecting the activities of expanded practice nurses within the interprofessional team on the intervention wards. The intervention will be implemented over a six-month period and compared with optimised care on the control wards. We will include people aged 65 years and older with existing cognitive impairment and/or at risk of delirium. The estimated sample size is 720 participants. The primary outcome is length of hospital stay. Secondary outcomes include prevalence of delirium, prevalence of agitation, sleep quality, and person-centred care. We will collect patient level data at six time points (t_1_ admission, t_2_ day 3, t_3_ day 7, t_4_ day 14, t_5_ discharge, t_6_ 30 days after discharge). For secondary outcomes at staff level, we will collect data before and after the intervention period. The process evaluation will examine degree and quality of implementation, mechanisms of change, and the context of the complex intervention. The economic evaluation will focus on costs from the hospital’s perspective.

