**Fig. 2 Fig2:**
[figure not shown]
Intervention components

Each intervention ward receives two EPN, qualified at level six of the European Qualifications Framework (bachelor’s degree or equivalent further education) [33]. EPN are integrated into the ward's work schedule and have one day each every two weeks for additional activities.

We developed different implementation strategies to prepare the field. EPN received a 200-h training regarding fundamentals of caring for people with cognitive impairment, principles of PCC, and Advanced Practice Nursing in six modules. In addition, EPN gained knowledge of established expanded nursing models in other hospitals during a 10-day internship. During the intervention period, we accompany the EPN fortnightly in two-hour coaching sessions for reflection and implementation support. We also train the interprofessional team at the beginning of the intervention phase on PCC principles and Advanced Practice Nursing during a one-hour kick-off meeting and through written information.

Team members of control wards provide optimised care with knowledge acquired through a one-time half-hour session and written information on PCC.

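### The economic evaluation declares a hospital perspective but counts DRG charges, which are hospital revenue, as hospital cost

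*Protocol article*

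**What the plan says.** The perspective is stated twice. The abstract has "The economic evaluation will focus on costs from the hospital’s perspective", and the section Economic evaluation has "We will perform a cost-consequence analysis from the hospital perspective". Potential cost savings are the third of the three aims under Objectives.

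The data are described under Economic evaluation, Data collection and management: "We will use claims data from the hospital to determine the potential cost savings of the intervention". On their content: "This data includes Diagnosis Related Groups (DRG) charges, length of hospital stay, cost weight, gender", followed by diagnosis codes. DRG charges are the only patient-level item in money. The other cost named for collection is training: "In addition, we will collect training costs consisting of salaries of the nursing staff, the costs of the lecturers", plus material costs.

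The total is built under Economic evaluation, Data analysis: "We will add the intervention costs (e.g., training costs) to the DRG charges of the intervention group". Mean totals are then compared between the arms by t-test, possibly after log-transformation. The same section compares length of stay and cost weight as items of their own.

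**The concern.** A charge in claims data is an amount the hospital invoices. For a payer it is a cost; for the hospital it is income. The plan adds an expense of the hospital (the intervention) to an income of the hospital (the charge), calls the sum total inpatient cost, and reads a lower sum as better.

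The study's hypothesis, given in the Background, is that fewer adverse events will shorten the stay. What that is worth to a hospital is the resources freed, set against any change in what it can bill. The planned total contains no term for freed resources, and it counts a change in billing in the direction opposite to its effect on the hospital's finances.

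The Discussion expects the findings to inform decisions at management and policy level. A hospital manager who takes the tested difference as the hospital's cost could turn down an intervention that frees resources, or adopt one because it lowers income.

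**Working it through.** **Plan's own figure.** The economic evaluation states no numerical target, so there is none to reproduce. The sample-size section supplies the inputs used here: a three-day shorter stay, and three wards of 120 patients per arm.

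**Step 1. What each quantity measures.** Per intervention patient relative to control, let
- D = change in DRG charge,
- S = value of the hospital resources saved,
- I = intervention cost.

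Then
- difference in the plan's total = D + I,
- difference in hospital resource cost = −S + I,
- change in the hospital's net position (income minus cost) = D + S − I.

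S is absent from the first line. D enters the first line as cost and the third as income, so a fall in charges (D < 0) improves the plan's result and worsens the hospital's position by the same amount. This follows from the definitions and needs no tariff rule.

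**Step 2. When the plan's total is right.** It equals the resource-cost difference only if D = −S, that is, if charges fall by exactly the resources saved. The net position then changes by −S + S − I = −I. In the one case where the plan's figure is a correct cost difference, the hospital keeps none of the saving.

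**Step 3. The planned effect.** 3 wards × 120 patients = 360, and 360 × 3 days = 1,080 bed-days. Write v for the fall in charge per day saved and c for the resource cost of a day. Then D = −3v and S = 3c, and
- plan = −3v + I,
- resource cost = −3c + I,
- net position = −3v + 3c − I.

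The article gives neither v nor c nor I.

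**Step 4. Illustration of sign only.** The values below are assumptions in arbitrary money units per patient.

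| v | c | I | plan | resource cost | net position |
|---|---|---|---|---|---|
| 0 | 300 | 100 | +100 | −800 | +800 |
| 100 | 300 | 100 | −200 | −800 | +500 |
| 300 | 300 | 100 | −800 | −800 | −100 |
| 300 | 100 | 100 | −800 | −200 | −700 |

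In the first row the hospital gains and the plan reports extra cost. In the last row it loses and the plan reports a saving. For v from 0 to 300, c from 100 to 600 and I from 0 to 300, the plan's difference runs from −900 to +300 and the net position from −900 to +1,800. The plan's difference depends on v and I alone and carries no information on c.

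**Step 5. Recurring intervention input.** The Intervention section gives each intervention ward two expanded practice nurses, so 3 × 2 = 6. They "have one day each every two weeks for additional activities" and have two-hour coaching every fortnight. Taking six months as 26 weeks gives 13 fortnights:
- release: 6 × 13 = 78 days,
- coaching, if all six attend each session: 13 × 2 h × 6 = 156 nurse-hours.

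The one-off input is 6 × 200 h = 1,200 training hours and 6 × 10 = 60 internship days. The recurring part is large enough to belong in I.

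**The case against.** **Saved days are not lost.** In a cost-consequence analysis the consequences stand beside the costs, and length of stay is one of the items compared. A three-day reduction would be reported in days, and a reader could apply a local day cost. This stands. It narrows the fault to the monetary line, but that line is the one called cost and tested.

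**Charges can stand in for cost.** They may do so if they follow resource use closely. The article does not say how the charge varies with stay or coding, so the substitution is unsupported. Step 2 shows that even a perfect match would not describe the hospital's gain.

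**Stronger readings.** A reader might infer that saved bed-days cannot show as a saving at all, or that the intervention arm must look dearer by construction. Both need a charge that is flat per case, which the documents do not state. The second also needs equal mean charges in the two arms apart from the intervention, which non-randomised wards do not guarantee. A reader might also infer that fewer coded complications would show as a false saving. The documents do not say that coding changes the charge, and fewer complications may also save real resources.

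**Recurring costs.** It is tempting to say that release and coaching time are left out. The wording in Data analysis gives training only as an example, and Table 2 already plans ongoing documentation of coaching contact hours and a logbook of the nurses' activities. Itemised costing may also sit in the full protocol. An omission is therefore not shown; naming these items would merely settle it.

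**Weight.** The economic evaluation accompanies an exploratory, feasibility-stage trial and touches neither the primary outcome nor safety. That limits the severity.

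**Conclusion.** The point holds in a limited form. The declared perspective and the cost measure contradict each other. Followed as written, the tested total is not hospital cost: it registers saved bed-days only through changes in charges, and it scores any fall in charges as a saving although hospital income falls by the same amount. Because perspective, data source and formula are all stated, this is not a matter of detail left out of an article.

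The conclusion rests on one reading, that DRG charges in hospital claims data are billed amounts, which is the ordinary meaning of the words.

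The size can be given in days only: 1,080 bed-days if the planned effect occurs in 360 patients. No euro amount can be derived from the documents, and neither the direction nor the extent of the error in the actual result can be predicted without the tariff rule and a day cost.

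**What to change.** In Economic evaluation, Data analysis, define hospital cost as resource use plus intervention cost. Resource use can be case-level cost where the controlling department holds it, or otherwise bed-days times a ward-day cost from that department. State that intervention cost includes the nurses' release time and the coaching time as well as training and internship, and show one-off and recurring parts separately. Report DRG charges and cost weight on a revenue line of the cost-consequence table, not summed with costs.

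The alternative is to keep charges and restate the perspective as the payer's in the abstract and in Economic evaluation. Intervention cost should then be added only as far as the payer bears it, and the result should not be described as a saving to the hospital.

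The first option costs one extra data item from the department that already delivers the claims, and the use of hours largely recorded for the process evaluation. Trial conduct does not change. Its drawback is that a ward-day average is only an approximation: it values every saved day alike, whatever that day really cost. The second option needs only rewording, but leaves the question of hospital savings unanswered.
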